#### Exclusion criteria

Patients aged 50 years or under on January 1st, 2006.Patients without a recording of TSH above 4.0 mIU/L between January 1st, 2006, and December 31st, 2021.Patients diagnosed with thyroid cancer, pituitary disease or hyperthyroidism.Patients prescribed medications such as amiodarone or lithium that can affect thyroid function.Patients who have undergone thyroid surgery or radioiodine treatment, suggesting previous thyroid dysfunction.Patients receiving a different form of thyroid replacement therapy to LT4, e.g. liothyronine or combination therapy with liothyronine and LT4.Patients with a baseline diagnosis of angina, myocardial infarction, peripheral vascular disease or stroke, where cardiovascular is the outcome variable.Patients with a baseline diagnosis of osteoporosis or fracture, where bone health is the outcome variable.

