**Methods:**

This project includes a retrospective cohort analysis and a target trial emulation study using electronic patient records collected between 2006 and 2021 and recorded in The Health Improvement Network database. The primary outcome of this study is to compare the cardiovascular outcomes of subclinical hypothyroid patients aged over 50 years treated with levothyroxine compared to those untreated. Secondary outcomes are bone health and all-cause mortality outcomes. Descriptive and inferential statistics will both be employed to analyse the data. Secondary analysis will explore confounding factors, including age, sex, smoking status, body mass index, co-morbidities, and levothyroxine dosage.

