## Methods/Design

### Study aims

The study aims to evaluate whether LT4 benefits patients aged over 50 years with marginally raised TSH. The null hypothesis is that SCH patients over 50 years of age have the same bone health and cardiovascular outcomes when prescribed LT4 compared to those not prescribed LT4. The alternative hypothesis is that SCH patients aged over 50 years of age have worse bone health and cardiovascular outcomes when prescribed LT4 than those who are not prescribed LT4.

The objectives of the study are:

1) To use electronic healthcare records to undertake a cohort study comparing the cardiovascular outcomes (incident diagnosis of angina, myocardial infarction, stroke, peripheral vascular disease and stent/revascularisation procedure) between patients over 50 years of age with mildly elevated TSH levels prescribed LT4 versus those not prescribed LT4.

2) To use electronic healthcare records to undertake a cohort study comparing the bone health outcomes (incident diagnosis of osteoporosis, fragility fractures) between patients over 50 years of age with mildly elevated TSH levels prescribed LT4 versus those not prescribed LT4.

3) To use electronic healthcare records to undertake a cohort study comparing all-cause mortality outcomes between patients over 50 years of age with mildly elevated TSH levels prescribed LT4 versus those not prescribed LT4.

4) To use electronic healthcare records to undertake a target trial emulation study comparing the cardiovascular outcomes (incident diagnosis of angina, myocardial infarction, stroke, peripheral vascular disease and stent/revascularisation procedure) between patients over 50 years of age with mildly elevated TSH levels prescribed LT4 versus those not prescribed LT4 [46].

5) To use electronic healthcare records to undertake a target trial emulation study comparing the bone health outcomes (incident diagnosis of osteoporosis, fragility fractures) between patients over 50 years of age with mildly elevated TSH levels prescribed LT4 versus those not prescribed LT4.

6) To use electronic healthcare records to undertake a target trial emulation study comparing all-cause mortality outcomes between patients over 50 years of age with mildly elevated TSH levels prescribed LT4 versus those not prescribed LT4.

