### Study setting

THIN captures clinical data from general practices across the UK, holding anonymised records of approximately 6% of the UK population from 850 general practices. THIN has over 25 years of data recorded. To ensure a complete and reliable dataset, this project will capture data between January 1st, 2006, and December 31st, 2021. Preliminary counts from THIN show 530,792 patients with a TSH greater than 4 mIU/L. Preliminary counts also show 258,868 patients diagnosed with hypothyroidism within the same period. The variables that will be captured from the THIN database are as follows:

sex,diagnosed with hypothyroidism,date of diagnosis of hypothyroidism,date LT4 treatment commenced,first and last recorded LT4 dose,co-morbidities (heart disease, asthma, chronic obstructive pulmonary disease, diabetes, chronic kidney disease, rheumatoid arthritis, depression, dementia, dyslipidaemia, osteoporosis, fragility fractures).date of diagnosis of co-morbidities,current and past medications,date of death (if applicable),TSH, fT4, thyroxine (T4), triiodothyronine (T3), and free triiodothyronine (fT3) levels,date of recorded TSH, fT4, T4, T3, and fT3 levels,thyroid peroxidase antibody status,body mass index (BMI) at entry and end of the study period,blood pressure,smoking status.

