### Statistical analysis

The sample size calculation is based on the primary outcome of determining a difference in cardiovascular outcomes between patients receiving LT4 or not. The TRUST study of 737 patients aged 65 years and older found a cardiovascular outcome rate of 4.9% in the treatment group and 5.4% in the placebo group. Therefore, based on these outcome rates, for the cohort study, the minimum sample size required is 82,118 patients. Of this sample, 41,059 patients will be prescribed LT4 and 41,059 patients will not be prescribed LT4. A matching ratio of 1:4 (treatment: no treatment) will be used for the target trial emulation study. Therefore, the sample size required is 129,020 patients, with 25,804 patients prescribed LT4 and 103,216 patients not prescribed LT4. This sample size provides a power of 0.9 and alpha of 5%. In both studies, if missing data occurs, multiple imputation methods will be used if up to 40% of the data is missing [47]. Otherwise, pairwise deletion will be used.

In the target trial emulation study, the causal contrasts of interest will be intention-to-treat effect. Chi-square analysis will be used to compare the categorical characteristics of the participants in both studies, such that a p-value of less than 0.05 will be considered significant. Descriptive statistics will be presented. In both studies, the frequency of hypothyroidism diagnosis, smoking status, sex, ethnicity, and location will be given for each group. Survival analysis methods, including Cox proportional hazard models and Kaplan-Meier curves, will be fitted to compare the time to outcome between the groups. The hazard ratios with their 95% confidence intervals will be given.

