Confounding bias, immortal time bias, and information bias will be adjusted for both the cohort and target trial emulation studies [48]. In addition, selection bias and attrition bias will be adjusted for in the target trial emulation study. Confounding factors include sex, BMI, co-morbidities, and smoking status. The adjustment for confounding factors will be done using inverse probability weighting in the target trial emulation study [49]. In both studies, subgroup analysis will be done for each cardiovascular and bone health outcome and each age group (51–60, 61–70, 71–80, 81–90, 91 + years). A subgroup analysis including patients with a TSH level between 4 0.0 mIU/L and the upper limit of their age range in the TEARS study will be carried out. Another subgroup analysis of patients who have had a TSH level of 10 mIU/L or above or not will be conducted. Also, sensitivity analysis will be undertaken in both studies for different TSH thresholds, as the standard threshold can differ between laboratories. This study will perform a secondary analysis based on baseline fT4 levels, comparing patients with a low normal versus high normal levels (below and above median levels at baseline, respectively).

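### The cardiovascular outcome counts incident stent/revascularisation, but a prior procedure is not among the baseline exclusions for that outcome

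*Protocol article*

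**What the plan says.** The abstract makes the cardiovascular comparison primary: "The primary outcome of this study is to compare the cardiovascular outcomes of subclinical hypothyroid patients aged over 50 years treated with levothyroxine". Under Study aims, objective 1 (cohort study) and objective 4 (target trial emulation) both define the outcome as "incident diagnosis of angina, myocardial infarction, stroke, peripheral vascular disease and stent/revascularisation procedure".

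Under Exclusion criteria, the cardiovascular item removes "Patients with a baseline diagnosis of angina, myocardial infarction, peripheral vascular disease or stroke, where cardiovascular is the outcome variable". The item for the bone outcome removes "Patients with a baseline diagnosis of osteoporosis or fracture, where bone health is the outcome variable".

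Three other statements bear on the point. Study setting lists the co-morbidities to be captured, beginning "co-morbidities (heart disease, asthma, chronic obstructive pulmonary disease, diabetes, chronic kidney disease, rheumatoid arthritis, depression, dementia, dyslipidaemia, osteoporosis, fragility fractures". Statistical analysis says "Confounding factors include sex, BMI, co-morbidities, and smoking status", and also that "subgroup analysis will be done for each cardiovascular and bone health outcome and each age group".

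**The concern.** An outcome described as incident needs a population free of that outcome at baseline. The protocol follows this principle for bone health, and for four of the five cardiovascular components. It does not follow it for stent/revascularisation. A patient with an earlier stent, angioplasty or bypass on record, and none of the four listed diagnoses, passes the criteria as printed. If that patient later has another procedure, or has angina or infarction coded for the first time, the event is counted as first cardiovascular disease when it is not.

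Two things are at stake. The first is the meaning of the endpoint, above all in the separate analysis of each cardiovascular outcome, where the procedure is an endpoint in its own right with no baseline exclusion for itself. The second is a possible disturbance of the treated v untreated contrast, if such patients are spread unevenly between the groups and adjustment does not capture them.

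**Working it through.** **1. Match the outcome to the exclusion, component by component.**

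| Outcome component (Study aims) | Excluded at baseline? |
|---|---|
| Angina | yes |
| Myocardial infarction | yes |
| Stroke | yes |
| Peripheral vascular disease | yes |
| Stent/revascularisation | **no** |
| Osteoporosis (bone) | yes |
| Fragility fracture (bone) | yes (any fracture) |

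The remaining inclusion and exclusion criteria concern age, TSH, thyroid and pituitary disease, interfering drugs, thyroid surgery or radioiodine, and the type of replacement therapy. None removes a patient with only a prior procedure code.

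**2. Reproduce the plan's own figure.** The sample size uses a trial that "found a cardiovascular outcome rate of 4.9% in the treatment group and 5.4% in the placebo group", with alpha 5% and power 0.9. For two proportions with pooled variance, two-sided, without continuity correction:

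n = [1.960·√(2·0.0515·0.9485) + 1.2816·√(0.049·0.951 + 0.054·0.946)]² / 0.005² ≈ 41,059.1,

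or 41,060 per group rounded up, against 41,059 stated. The same method at 1:4 gives 25,805 treated, against 25,804 stated. The sample-size arithmetic is sound and does not depend on the present point. The planned risk ratio is 4.9/5.4 = 0.91.

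**3. Share of events from procedure-only patients.** The document gives neither their share *f* of the cohort nor their event risk *q*. Both are assumed here, with a 5% risk in everyone else (a round figure near the 4.9% and 5.4% above).

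Share = f·q / [(1 − f)·0.05 + f·q]

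| f | q = 10% | q = 30% |
|---|---|---|
| 0.5% | 0.0005/0.05025 = 1.0% | 0.0015/0.05125 = 2.9% |
| 1% | 0.0010/0.0505 = 2.0% | 0.0030/0.0525 = 5.7% |
| 2% | 0.0020/0.0510 = 3.9% | 0.0060/0.0550 = 10.9% |

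**4. Unadjusted risk ratio when the true effect is nil.** This is the treated mixture risk divided by the untreated mixture risk.

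| Prevalence, untreated v treated | q = 10% | q = 30% |
|---|---|---|
| equal | 1 | 1 |
| 1% v 0.5% | 0.05025/0.0505 = 0.995 | 0.05125/0.0525 = 0.98 |
| 2% v 1% | 0.0505/0.0510 = 0.990 | 0.0525/0.0550 = 0.95 |

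If the imbalance runs the other way, the ratios invert (0.0550/0.0525 = 1.05 at the extreme). On the log scale the planned effect is ln(4.9/5.4) = −0.097. The extreme value is ln(0.0525/0.0550) = −0.047, about half of it. The 0.98 is about a quarter, and the two 10%-risk values are about a tenth and a twentieth.

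**5. Dilution with equal prevalence.** Take 4.9% and 5.4% in the other patients, and the same q in both groups for procedure-only patients. Power at 41,059 per group then falls from 0.900 to 0.896 (f = 0.5%, q = 10%), and to 0.860 at the extreme (f = 2%, q = 30%).

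**The case against.** The strongest reply is that the affected group is only a residue. Revascularisation is normally done for angina, infarction or peripheral vascular disease, so most patients with a procedure would already be excluded on one of those diagnoses. This stands, and it limits the size. It leaves eligibility dependent on complete diagnosis coding, which the protocol does not take for granted elsewhere: its feasibility work found 622 patients on LT4 against 465 coded as hypothyroid. That evidence concerns thyroid codes only.

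A second reply is that a code list in the full protocol may treat a stent as evidence of one of the four diagnoses. That is possible and cannot be checked from the article. It does not remove the disagreement between two lists that the article prints.

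A third reply is planned adjustment. Heart disease is captured as a co-morbidity, co-morbidities are named confounders, and the emulation uses inverse probability weighting. If prior procedures are mapped to heart disease, which is not stated, much of any imbalance would be addressed. The ratios in step 4 are therefore unadjusted upper illustrations. Adjustment does not take these patients out of the risk set or make a repeat procedure incident.

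A reader might go further and infer that the omission biases the primary contrast by an amount comparable with the planned effect. The documents do not support that. The 30% risk, the 2% share and the two-fold imbalance are all assumptions. Even together they give about half the planned log effect before adjustment, and equal prevalence gives none.

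**Conclusion.** The mismatch is certain from the text: five incident components, four of them excluded at baseline, and no other criterion that fills the gap. Its consequence for the definition of the endpoint is real, and clearest in the analysis of stent/revascularisation as a separate outcome, where the other four components do not dilute it.

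Its numerical effect on the primary comparison is uncertain and probably small. Under assumed shares of 0.5% to 2% and risks of 10% to 30%, procedure-only patients would supply about 1% to 11% of events. The unadjusted risk ratio would move by anything from nothing to about 0.95 (or 1.05 if the imbalance is reversed). The document gives no basis for choosing within those ranges or for predicting the direction. This is a consistency correction worth making before the cohort is extracted. It is not evidence that the primary result would be materially biased, and it leaves the sample-size calculation as it is.

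**What to change.** Add prior stent/revascularisation procedure to the baseline exclusion that applies where cardiovascular disease is the outcome, in both the cohort study and the emulation. Define it with the same code list as the outcome component, including peripheral or carotid procedures if those count as outcome events, so that exclusion and outcome match component for component. If the full protocol's code lists already treat such procedures as a baseline diagnosis, a sentence saying so would be enough.

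The cost is one phrase, a code list that the outcome needs anyway, and the loss of a few patients. Reporting how many are removed on this ground alone would show how much the point mattered.

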The current research group has completed a National Institute for Health and Care Research (NIHR) Research for Patient Benefit study (Study of Optimal Replacement of Thyroxine in ElDerly (SORTED) – a feasibility study: Ref: PB-PG-0610-22139) and has demonstrated that older people can tolerate a lower dose of LT4 and hence higher TSH levels [45]. The work done in 2016 explored the relationship between the three variables: diagnosis of hypothyroidism, TSH measurement, and LT4 treatment. A feasibility analysis at one large rural general practice in Northumberland, England, with a practice list size of 11,752 found that 465 patients had been diagnosed with hypothyroidism. The prevalence of hypothyroidism at the practice was 4%, and the highest prevalence was in the 81–90 years age category, at 9.85%. The female-to-male ratio with hypothyroidism at the practice was 4.4:1.0, such that 379 females had been diagnosed. Despite 465 patients diagnosed with hypothyroidism (Read Coded), 622 patients received treatment with LT4. This is an excess of 157 patients receiving LT4 without a diagnosis of hypothyroidism. This may represent a proportion of SCH patients that are not Read Coded as hypothyroid but are receiving treatment. It is also possible that a small proportion of these patients are hyperthyroid patients receiving block and replace treatment or patients with pituitary disorders. Alternatively, some patients may report symptoms suggestive of hypothyroidism but still have normal serum thyroid function tests and receive LT4 therapy in contravention of accepted clinical practice and guidelines. For this reason, our search strategy centres upon the TSH values recorded in the database rather than a diagnosis. Between 2003 and 2015, 215 (1.9%) patients were recorded as having an age-specific index TSH as mildly elevated, in line with the TEARS study. Of those, 39% were untreated, and 61% were treated with varying degrees of treatment length. This feasibility work concludes that 53% of the treated patients may have been over-diagnosed due to their TSH level being within the range of 4.0 mIU/L and the upper TSH limit given by the TEARS study [13].

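### Freedom from cardiovascular and bone disease at baseline is judged by recorded diagnosis only, and captured prescriptions are neither used to detect prevalent outcome disease nor named as confounders

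*Protocol article*

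**What the plan says.** **Outcomes.** The Study aims section of the protocol article defines the "bone health outcomes (incident diagnosis of osteoporosis, fragility fractures"). The cardiovascular outcome is likewise an incident diagnosis of angina, myocardial infarction, stroke or peripheral vascular disease, or a stent or revascularisation procedure.

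**Baseline exclusions.** The Exclusion criteria remove "Patients with a baseline diagnosis of osteoporosis or fracture, where bone health is the outcome variable" and "Patients with a baseline diagnosis of angina, myocardial infarction, peripheral vascular disease or stroke, where cardiovascular is the outcome variable". Neither rule mentions treatment.

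**Prescriptions.** The Study setting section lists "current and past medications" among the captured variables. The Exclusion criteria use prescriptions twice, for "Patients prescribed medications such as amiodarone or lithium that can affect thyroid function" and for "Patients receiving a different form of thyroid replacement therapy to LT4".

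**Confounders.** The Statistical analysis section states: "Confounding factors include sex, BMI, co-morbidities, and smoking status". The Methods paragraph of the Abstract adds age and levothyroxine dosage. Neither list names a background drug.

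**Feasibility work.** The Background reports 465 patients Read Coded as hypothyroid and 622 on levothyroxine in one practice: "This is an excess of 157 patients receiving LT4 without a diagnosis of hypothyroidism". The protocol therefore searches for its study population by TSH value, not by diagnosis.

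**The concern.** An incident-diagnosis outcome is only as good as the baseline rule that removes existing disease. In routine records, treatment may begin before a diagnosis is coded, or without one being coded. A patient who is already on an osteoporosis drug, or on a nitrate for angina, but who has no recorded diagnosis passes the exclusion as worded. If the diagnosis is entered during follow-up, old disease is counted as a new event.

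The consequence depends on how late coding is distributed:

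- If it is equally frequent in both groups, it adds the same number of false events to each and pulls the hazard ratio towards 1.
- If levothyroxine patients are reviewed more often, which is an assumption, more late coding would fall in that group. This would look like harm from treatment, which is the direction of the alternative hypothesis in Study aims.

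The second strand is confounding. Statins, antiplatelets, anticoagulants, systemic glucocorticoids and menopausal hormone therapy all act on the endpoints. If their baseline use differs between treated and untreated patients after adjustment for the named factors, the difference remains in the hazard ratio.

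**Working it through.** **1. What the rules do when set side by side.** The outcome is an incident diagnosis, the baseline screen is a baseline diagnosis, and the medication field is available. The protocol writes a prescription rule where it wants one (thyroid-active drugs, other thyroid hormone). It writes a diagnosis rule for the outcome diseases. Followed as worded, the text admits treated but uncoded disease.

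**2. Which outcomes are exposed.** Late coding can affect conditions that are recorded at some point after they begin: osteoporosis, angina and peripheral vascular disease. A myocardial infarction, stroke or new fracture in follow-up is a dated event. It may be a recurrence, but it did happen in follow-up.

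**3. The feasibility figure.** 622 − 465 = 157, and 157/622 = 25.2%. This is a net difference. It equals the uncoded share of treated patients only if all 465 coded patients were treated. If 90% were treated, the share would be (622 − 0.9 × 465)/622 = 203.5/622 = 32.7%. In either case it describes hypothyroidism codes in one practice. It shows that treatment can exist without the code, and gives no rate for any cardiovascular or bone condition.

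**4. The planning figures.** The Statistical analysis section uses 4.9% (treated) and 5.4% (untreated), power 0.9 and alpha 5%. The two-sided comparison of two proportions, with pooled variance under the null and no continuity correction, gives

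n = [1.960 × √(2 × 0.0515 × 0.9485) + 1.282 × √(0.049 × 0.951 + 0.054 × 0.946)]² / 0.005² ≈ 41,059 per group.

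This reproduces the cohort figure. The planned risk ratio is 4.9/5.4 = 0.907.

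**5. Illustration on assumed inputs.** Let u be the share of each group with uncoded prevalent disease and c the share of these first coded in follow-up. The documents give neither value. The observed rate in each group is q = p(1 − u) + u·c, and the share of treated-group events that are prevalent disease is u·c/q. Power is for 41,059 per group.

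| u | c | Treated | Untreated | Risk ratio | Prevalent share of treated events | Power |
|---|---|---|---|---|---|---|
| 0 | – | 4.90% | 5.40% | 0.907 | 0% | 0.90 |
| 1% | 10% | 4.95% | 5.45% | 0.909 | 2% | 0.89 |
| 2% | 30% | 5.40% | 5.89% | 0.917 | 11% | 0.86 |
| 5% | 30% | 6.16% | 6.63% | 0.928 | 24% | 0.795 |

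Suppose instead, as an extreme, that late coding occurs only in the treated group and the untreated rate stays at 5.4%. The same three inputs then give risk ratios of 0.917, 1.00 and 1.14.

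This uses the cardiovascular planning rates. The article gives no bone event rate, so no corresponding table can be built for the bone outcome.

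**The case against.** **Definitions may sit elsewhere.** The exclusions speak of a diagnosis, and how a diagnosis is ascertained is commonly left by an article to a fuller document. Capturing medications is compatible with using them as supporting evidence. This limits the point: the absence of code lists is no fault. What remains is that a stated eligibility rule is framed by diagnosis, in a list that uses prescriptions elsewhere.

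**Prescriptions are not ignored.** A reader might infer that recorded drugs play no part in the plan. That would be wrong, because two exclusions rest on them. The gap is confined to detecting prevalent outcome disease and to the named confounders.

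**The 25% does not carry over.** A reader might take 157/622 as a measure of under-coding in general. The documents do not support that. The Background offers several explanations for the excess: treated subclinical disease not coded as hypothyroid, block-and-replace treatment, pituitary disorders, and symptoms with normal thyroid tests. In the last three, the missing code may be correct. Nor does searching by TSH reject diagnosis codes in general, since the study condition is a laboratory finding.

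**Confounder lists are open.** The Statistical analysis section says that confounders include four items. The adjusted co-morbidities, together with the captured dyslipidaemia, heart disease, rheumatoid arthritis and chronic lung disease, cover many indications for these drugs. The section also promises adjustment for information bias in both studies. This stands in part and makes the confounder strand weaker than the eligibility strand. An indication is not the same as being treated, however, and the article ties no stated step to late coding.

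**Conclusion.** The point holds as a weakness in a stated eligibility rule, with a cheap remedy. As worded, patients treated before baseline for osteoporosis or angina without a recorded diagnosis may enter and later be counted as incident. Endpoint-active background drugs are captured but not named for adjustment.

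The documents do not show that this misclassification occurs, and they allow no estimate of its size or direction. The illustrative range rests wholly on assumed values of u and c applied to cardiovascular rates. At its low end the effect is negligible (0.907 to 0.909). It deserves attention because the planned difference is only 0.5 percentage points, so modest contamination would cost power. The concern is greatest for osteoporosis, angina and peripheral vascular disease, and slight for infarction, stroke and new fracture.

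**What to change.** 1. Extend the two baseline exclusions to a prescription, before the start of follow-up, of a drug specific to the condition: osteoporosis drugs for the bone analysis and antianginal nitrates for the cardiovascular analysis. If the main definition is to stay as it is, run this version as a prespecified sensitivity analysis in both studies. Nitrates address angina only, so uncoded peripheral vascular disease would remain.
2. Name baseline use of statins, antiplatelets, anticoagulants, systemic glucocorticoids and menopausal hormone therapy as covariates, taken from the medication field already captured. Enter them in the weight model of the target trial emulation and in the Cox model of the cohort study.

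**Cost.** The work is drug code lists applied to data already planned for extraction. The loss of eligible patients should be small against the preliminary count of 530,792 with a raised TSH, although the documents do not allow it to be counted. Some patients given these drugs for prevention, who do not have the disease, would be excluded. That is a reason to report results under both definitions.
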